#### Therapist training

The PI has experience delivering didactic trainings to criminal legal staff audiences and will plan to consult as needed to ensure appropriate delivery and receive feedback on content and structure. The PI and graduate student delivering the client interventions have experience delivering behavioral interventions as well as specific training in acceptance and commitment therapy. The PI is a licensed clinical psychologist and the trainee has two years of clinical experience. The PI and trainee will engage in regular consultation with the intervention developer ([name]) who will review video recordings of the training to provide feedback on clinical skills and content delivery. Treatment fidelity scales and interventionist training procedures will be developed throughout the study to facilitate fidelity rating of therapists.

### Participants and procedures

#### CSTARR-staff

The CSTARR-staff intervention is scheduled according to each county’s court calendar to facilitate TN-ROCS staff availability. To recruit our target sample of 72 staff across 6 counties, the judge in each county will distribute an advertisement for the CSTARR-staff training that includes a link to register. Staff will be strongly encouraged to participate but not required to. When staff register, they will automatically be sent the training details (via Zoom) and then emailed an invitation to complete the online baseline survey which includes the informed consent. Staff are permitted to register and attend the training without completing the baseline survey. Any staff affiliated with the TN-ROCS program who have interacted (either virtually or in- person) with a TN-ROCS client in the past 90 days are eligible to participate. Staff are asked to complete an anonymous feedback survey during the last 10 min of the training and are sent a link to complete the post-test survey at that time. Staff are automatically emailed with the one-month and three-month follow-up survey links. For completing the pre- and post-test surveys, staff receive a $5 e-gift card. For the follow-up surveys, they are emailed a $10 gift card. We anticipate retaining 75% of staff by the 3-month follow up. The training is audio-recorded. We will continue to approach staff for follow-up regardless of missing data at a prior timepoint. Email and phone call reminders will be used to increase completion of online surveys.

#### CSTARR-client

To recruit our target sample of 72 TN-ROCS clients across 6 counties (i.e., approximately 12 per county), each county’s CJL will distribute a study advertisement when doing treatment intakes with new clients. CJLs (and judges) will strongly encourage clients to consider participating but it will not be required as part of their involvement in TN-ROCS. Interested clients sign a recruitment waiver so their contact details can be released to the research team. The Project Coordinator then contacts clients via phone to have an in-depth discussion of procedures, risks, benefits, and human subjects protections as part of the informed consent process. Consented clients then proceed to complete their baseline interview over the phone. Any TN-ROCS clients (i.e., arrested, have evidence of substance use problems, are accepted into the TN-ROCS program), will be eligible except those deemed by the CJL to have debilitating mental illness or violence risk. There are no exclusion criteria around stigma (e.g., those reporting low self-stigma) in order to gauge CSTARR utility for all clients. At the end of each intervention session, clients are asked to complete an anonymous online feedback form, and their post-test survey (completed over the phone with a research assistant) is scheduled to take place immediately after the last intervention session. Participants receive a $5 giftcard for the baseline and post-test interviews, and a $10 gift card for the 1- and 3-month follow up assessments. To offset the time and logistical burden of completing the intervention, participants will receive up to $30 in gift cards if they attend the entire intervention. All group sessions are audio-recorded. We anticipate retaining 75% of clients across the 3 sessions and 50% by the 3-month follow-up. We continue to approach clients for follow-up regardless of missing data at a prior timepoint. Phone calls, texts, and/or email reminders are used to increase completion of surveys.

#### Focus group

A 1.5 h focus group with approximately 10 key stakeholders (e.g., judges, CJLs, administrators) who participated in the CSTARR-staff training will occur at the end of the study. The focus group will be led using a semi-structured question guide aimed at understanding 1) feedback on intervention delivery 2) discussion of barriers, 3) suggestions for improvement, and 4) ideas for sustainment. Informed consent will involve explaining focus group procedures, risks/benefits, and incentives for participation ($20 giftcard). The group will be audio-recorded to facilitate transcription. Data will be used to understand barriers and facilitators of implementation to inform future study planning.

### Staff assessments

Demographic data on staff (i.e., age, sex, race, education level, agency, position, job tenure, interpersonal contact with people who have substance use and/or criminal backgrounds, and organizational stress) is gathered as part of the baseline assessment.

#### Primary staff outcomes

We will examine change from the baseline to the three-month follow-up timepoint in the following measures:Perspectives on Stigma Reduction. The Perspectives on Stigma Reduction scale (PSR) is a 24-item internally developed measure that assesses perspectives on stigma (e.g., importance, impact on people involved in the criminal legal system) and stigma reduction strategies (e.g., openness to learning new strategies, use of nonjudgmental behaviors), among criminal legal professionals. 20 of the items are rated on Likert scales ranging from 1 (strongly disagree) to 9 (strongly agree), and 4 items are rated on a scale from 1 (0% of the time) to 9 (100% of the time). Items with the same response scales are summed to create total composite scores. Higher scores indicate more favorable views about stigma reduction.Difference and Disdain. The Difference and Disdain scale (DaD) (Corrigan et al., 2015b) is a 9-item measure that assesses how individuals view others in stigmatized groups compared to the general population. Responses are rated on a scale from 1 to 9, where 1 represents a belief that stigmatized people are similar to/favorable compared to others in the general population and 9 represents a belief that they are different from/unfavorable compared to the general population. We adapted this measure to ask about people with substance use problems and then criminal involvement (18 items total). Each scale ranges from 9–81 with higher scores indicating more differences/disdain. This measure has been shown to be valid for assessing public stigma in multiple studies (Corrigan, 2017; Corrigan et al., 2021).Social Distance. We use 10 items to assess desired social distance from people with a criminal background (separately asking about violent and nonviolent criminal histories) and 5 parallel items to assess desired social distance from people with histories of addiction. Items were adapted from the Bogardus social distance measure (Bogardus, 1933) to capture how staff would feel about interacting with (e.g., working, living next to, talking to, marrying) people with these backgrounds. Responses are rated on a Likert scale ranging from very uncomfortable to very comfortable, with the total score ranging from 10 to 50. Higher scores indicate less desired social distance. Variations of the Bogardus social distance items have been used widely and demonstrate good reliability and validity among various samples (Compton et al., 2006; Geisinger, 2010).Stigmatizing Attitudes Toward Criminal Involvement. The Attitudes Toward Prisoners scale (ATP) (Melvin et al., 1985) is a 36-item measure that assesses attitudes, beliefs, and negative stereotypes about “prisoners,” with responses rated on 5 point Likert scale from disagree strongly to agree strongly. We changed the word prisoners to “justice-involved people” throughout the scale to remove stigmatizing language but also because the staff we are targeting primarily work with people who are not currently incarcerated. Negatively worded statements are reverse coded for a summed total score ranging from 36 to 180. Higher scores indicate more positive attitudes toward people involved in the criminal legal system. The ATP has been used widely with criminal legal staff samples and demonstrates good internal consistency and validity (Kjelsberg et al., 2007; Ware et al., 2012).Beliefs About Addiction. The Addiction Beliefs Inventory (ABI) (Luke et al., 2002) is a 30-item measure containing 8 subscales that assess how people think about substance use, including beliefs about controllability, the disease model of addiction and genetic susceptibility, the need for professional treatment, how responsible someone with substance use is for their actions and recovery, self-medication, and beliefs about addiction being a moral weakness. Responses are rated on a 5-point Likert scale ranging from strongly disagree to strongly agree, with higher scores representing more agreement with the beliefs represented in the subscale. The ABI is often analyzed as subscales rather than a total score and demonstrates acceptable reliability and validity in multiple studies (Jordan et al., 2002; Luke et al., 2002).Opinions about Medication for Opioid Use. An adapted version of the Opinions about Medication-Assisted Treatment scale (aOAMAT) (Friedmann et al., 2016) will be used to evaluate how staff think about the treatment of OUD with methadone and buprenorphine among legally-involved populations. Responses are rated on a 6-point Likert scale (1 = strongly disagree, 5 = strongly agree, and we added a sixth response option if they had never heard of the medications). Methadone and buprenorphine were included in the same item to reduce the measure’s length, and naltrexone was not included (e.g., “Methadone and/or buprenorphine should be available as a lifelong treatment option”). This collapsed the 18 original items into 9; 2 additional items were added regarding the administration of medications during incarceration. This adapted measure has been shown to be reliable and valid with criminal legal staff ([name] et al., 2022).

#### Secondary staff outcomes

We will examine change from the baseline to the 3-month follow-up timepoint in the Dual-Relationship Inventory-Short Form (DRI-SF) (Gochyyev & Skeem, 2019), a 9-item measure adapted from the DRI and DRI-revised (Skeem et al., 2007) that was originally designed to be used in parallel forms with probation officers and their clients. The DRI assesses qualities of the relationship and working alliance between probation officers and clients. Responses are rated on a scale ranging from 1 (never) to 7 (always), with total scores ranging from 9 to 63. Higher scores indicate better relationships with clients. The DRI-Revised has been shown to be valid and internally consistent in a sample of probation officers and clients (Skeem et al., 2007). The DRI-SF has psychometrically sound properties comparable to the original DRI-R and has been validated in samples of probation officers and treatment staff (Gochyyev & Skeem, 2019).

#### Staff implementation outcomes

Feasibility will be assessed by examining intervention recruitment and retention rates (i.e., including people who leave the intervention prematurely) as well as survey attrition. We will use two measures to assess implementation outcomes. The first is a set of 12 internally developed items that are administered in an anonymous survey after the CSTARR-staff training. Items ask about comfort level with the material, how useful and relevant the training was, how likely staff are to use stigma reduction strategies, and how likely staff would be to recommend the training. Responses are rated on Likert scales ranging from 1 to 5, with total scores ranging from 12 to 60 and higher scores indicating more acceptability, and there are open-ended questions asking about suggestions for improvement. We will also use a 12-item measure that captures whether staff value CSTARR and how they feel about its implementation after the training.

### Client assessments

To characterize the client sample, we will gather data on sociodemographics (e.g., age, sex, race, education level, employment and housing situation) as well as substance use severity, criminal behavior/arrests, and substance use treatment experience as part of the baseline assessment.

#### Primary client outcomes

We will examine change from the baseline to the 3-month follow-up timepoint in the following measures:Self-stigma. We will use the Substance Abuse Self-Stigma Scale (SASS) ([name] et al., 2013) to assess self-stigma associated with substance use and criminal involvement. The SASS is a 41-item measure that assesses self-devaluation, fear of experiencing stigma, avoidance of stigma, and values disengagement among people with substance use problems. Responses are rated on a scale from 1 (never or almost never) to 5 (very often), with total scores ranging from 41 to 205 and higher scores indicating more self-stigma. We adapted this measure to ask about both criminal involvement and substance use stigma within the items in this measure (e.g., “People think I’m worthless if they know about my substance use or criminal history”). The SASS scale has been shown to be reliable and valid for assessing self-stigma among people with substance use problems (Brown et al., 2015; [name] et al., 2013).Shame. The Internalized Shame Scale (ISS) (Cook (n.d.)) is a 24-item measure that includes shame-related thoughts and experiences, which are considered central to self-stigma. Responses are rated from 0 to 4, where 0 is never and 4 is almost always, with the total score ranging from 40–120 and higher scores indicating more internalized shame. The ISS has been used to track changes in shame across clinical interventions, including ACT for substance use self-stigma ([name] et al., 2013) and is shown to be reliable and valid in a variety of clinical and non-clinical samples (Goffnett et al., 2020; Rybak & Brown, 1996).Self-efficacy. We use a 1-item internally developed measure to assess the degree to which clients feel they can cope with unfair judgments from the community regarding their substance use or criminal history. The item is rated on a scale from 1 to 10, with 1 being lowest expectation of success and 10 being the highest expectation of success.Coping skills. We use 28 items from the Dialectical Behavior Therapy Ways of Coping Checklist (DBT-WCCL) (Neacsiu et al., 2010) to assess client use of specific skills being taught in the CSTARR-client intervention. The DBT-WCCL is originally a 59-item measure that captures client use of adaptive and maladaptive coping skills and is widely used among people attending DBT skills interventions, which is another third-wave behavioral therapy similar to ACT. This measure has been used to assess improvement across treatment among people with various degrees/severity of mental illness (Brown et al., 2019; Kells et al., 2020; Stein et al., 2016). We utilize items that capture skills being taught in CSTARR-client (e.g., engaging in valued actions, acceptance of thoughts and feelings, emotion regulation techniques such as relaxation) as well as maladaptive coping skills we believe CSTARR-client may reduce, such as externalization of blame, avoidance, and social withdrawal/isolation.

#### Secondary client outcomes

We ask clients whether or not they are still enrolled in the TN-ROCS program at the 1- and 3-month follow-up timepoints and the types of treatment they are engaged in (e.g., outpatient, medications). We also assess for instances of substance use, criminal involvement leading to arrest, positive urine drug screens, and disciplinary infractions that have occurred during treatment. If we are unable to contact participants at follow-up, we ask CJLs whether clients are still currently enrolled in the TN-ROCS program and if not, record the reason for dropout.

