### Study design overview

This study plans to recruit approximately 72 criminal legal staff and 72 individuals involved in the criminal legal system across 6 counties (i.e., 12 per county) engaged with an incarceration diversion program called the Tennessee Recovery Oriented Compliance Strategy (TN-ROCS). Interventions for staff (1 4-h session for all staff in a county) and clients (multiple group sessions with 4–6 clients per group, per county) are to be delivered over the course of 12 months, with the staff interventions occurring first, followed by the client interventions in each county. The primary goal of this pilot study is to gather data on feasibility and acceptability of the interventions with staff and clients. The secondary goal is to examine preliminary effectiveness by analyzing change in client-level and staff-level outcomes of interest across baseline, post-test, one-month, and 3-month timepoints. We also aim to evaluate data on clients’ program-level outcomes, such as continued engagement in the TN-ROCS treatment program as well as disciplinary infractions and substance use that occurs during treatment. We utilized an open trial for this study due to our main focus on feasibility; we decided against having a comparator condition because clustering of clients and staff within counties would have necessitated a larger sample size than was feasible to recruit during the study period. In addition to the study activities described above, we will hold a focus group in each county at the end of the study to discuss implementation facilitators and barriers, as well as revision of implementation strategies moving forward.

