### Setting

CSTARR-staff and CSTARR-client are being delivered within the infrastructure of the TN-ROCS program, which is a drug recovery court (incarceration diversion) program operating in select counties in Tennessee. TN-ROCS was developed by Judge [name], who is a community leader and primary person facilitating stakeholder buy-in and engagement with this project. We chose this program because it allowed us to recruit multiple types of criminal legal professionals and their clients within a single program infrastructure to implement both levels of stigma interventions. TN-ROCS coordinates staff from multiple sectors (i.e., courts, detention, probation, treatment) into a unified care and judicial oversight approach for legally-involved people with substance use disorders. Upon arrest, individuals are identified as potentially eligible for TN-ROCS if substance use problems are deemed relevant to their legal involvement. A program intake is completed with a mental health treatment staff called a criminal justice liaison (CJL) during initial incarceration and a report including treatment recommendations is then reviewed by the judge who makes a final determination about acceptance into TN-ROCS. Clients accepted into the program are released and sent to an appropriate treatment setting based on their substance use needs (e.g., inpatient, residential, outpatient, medication). TN-ROCS clients appear before the judge and other team members (e.g., attorney, probation officer, treatment staff) regularly to ensure compliance with treatment. Sanctions (e.g., jail time) are used as needed to address non-compliance. Clients are typically enrolled in TN-ROCS for one year or longer.

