#### Effectiveness

Pre- to post- change in staff and client assessments will be analyzed using repeated measures factorial ANOVAs that compare pre, post-, 1-month, and 3-month follow-up data for clients and staff. Tukey’s posthoc comparisons will be used to pinpoint significant mean differences between timepoints. We will examine main and interaction effects to test whether mean differences in staff assessments depend on type of profession (assuming adequate sample sizes). Omega squared effect size estimates will be computed. We will control for relevant staff- and client-level variables. Additional analyses may include testing whether client and staff change scores (3-month survey score subtracted from pre-test) predict TN-ROCS program-level outcomes such as retention and disciplinary infractions. Significant effects will be designated by *p* < 0.10 and meaningful effect size estimates.

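### Limiting client events to those during treatment leaves out substance use, and probably arrest, after a client leaves TN-ROCS but is still interviewed

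*Protocol article*

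**What the plan says.** Two sections set the period over which client events are recorded. The Study design overview names the program-level outcomes as continued engagement in TN-ROCS together with "disciplinary infractions and substance use that occurs during treatment". Secondary client outcomes gives a longer list: "We also assess for instances of substance use, criminal involvement leading to arrest", followed by "positive urine drug screens, and disciplinary infractions that have occurred during treatment". Nothing in the document extends recording past the end of treatment.

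Enrolment is collected separately: "We ask clients whether or not they are still enrolled in the TN-ROCS program at the 1- and 3-month follow-up timepoints". For clients who cannot be contacted, "we ask CJLs whether clients are still currently enrolled in the TN-ROCS program and if not, record the reason for dropout"; no events are requested from the criminal justice liaison (CJL).

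Interviews do not depend on enrolment. The CSTARR-client section says: "We continue to approach clients for follow-up regardless of missing data at a prior timepoint". The Effectiveness section adds, as an optional analysis, that change scores may be tested to see whether they "predict TN-ROCS program-level outcomes such as retention and disciplinary infractions".

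**The concern.** The recording period depends on something that happens after baseline. The plan anticipates departure, since it asks about enrolment twice and records reasons for dropout. The Setting section says enrolment typically lasts a year or longer, so leaving within 3 months is early.

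Leaving is also plausibly linked to the behaviour being measured. Clients are reviewed regularly for compliance and "Sanctions (e.g., jail time) are used as needed to address non-compliance". The protocol does not say that expulsion follows infractions, so this link is an inference.

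If it holds, the clients doing worst have the shortest recording period, although some can still be asked about the whole 3 months. Reported levels of substance use and arrest would then be too low among the clients interviewed. The results are meant to inform a larger randomized trial, which could inherit the definition.

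**Working it through.** **Which outcomes the limit reaches**

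| Outcome | Study design overview | Secondary client outcomes | Can it occur after exit? |
|---|---|---|---|
| Substance use | limit explicit | limit if the closing clause governs the whole list | yes |
| Arrest | not named | same condition | yes |
| Positive urine screens | not named | same condition | program screens need enrolment |
| Disciplinary infractions | limit explicit | limit explicit | no |

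The wording therefore excludes real events for substance use (explicitly) and arrest (on the natural reading). For infractions and program screens it excludes nothing. The issue there is only that clients have unequal time at risk.

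**Which clients are affected.** The CSTARR-client section expects 50% retention by 3 months: 72 × 0.50 = 36 clients interviewed. The other 36 have no 3-month self-reported events, so theirs are missing. The understatement concerns only leavers among the roughly 36 who are reached. Their number is not given.

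**Size, under assumptions.** The plan states no figure to reproduce, and every rate below is assumed. Let d be the share of interviewed clients who left, r the leavers' event rate relative to stayers (stayers at 1 event per month), the window 3 months, and exit at 1.5 months.

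- True mean = 3(1 − d) + 3rd
- Recorded mean = 3(1 − d) + 1.5rd
- Understatement = 1.5rd / true mean

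| d | Clients of 36 | r = 1: true / recorded | Understated by | r = 3: true / recorded | Understated by |
|---|---|---|---|---|---|
| 10% | 3.6 | 3.00 / 2.85 | 5% | 3.60 / 3.15 | 12.5% |
| 25% | 9 | 3.00 / 2.625 | 12.5% | 4.50 / 3.375 | 25% |
| 40% | 14.4 | 3.00 / 2.40 | 20% | 5.40 / 3.60 | 33% |

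**One client.** A stayer at 1 event per month has 3 × 1 = 3.0 expected events. A leaver at twice that rate has 2 × 3 = 6.0 over the full window, but in treatment only 1.0, 2.0 or 4.0 when leaving at 0.5, 1 or 2 months. If a recorded event triggers the exit, adding it gives 2.0, 3.0 or 5.0. So the leaver may look better than the stayer, level, or worse. A reversed ranking is possible but not assured; the shortfall against 6.0 is present in every case.

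**Yes/no scoring.** Truncation does not depend on counting. With Poisson events at 1 per month, the chance of at least one event is 1 − e^(−3) = 0.95 over 3 months, and 1 − e^(−0.5) = 0.39 when recording stops at 0.5 month.

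**The case against.** Most of the opposing case stands.

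- **Scoring.** The protocol says only that instances are assessed. It fixes no count, yes/no or rate rule. A reader might infer that an early leaver is scored as having a low count, or as having no further events; no rule says so. Only the recording limit is stated.
- **Scope of the wording.** The closing clause in Secondary client outcomes could attach to infractions alone, which leaves arrests and screens open. Treatment is also undefined: clients are asked about TN-ROCS enrolment and, separately, about types of treatment, so someone who has left TN-ROCS may still be in treatment.
- **Exit is not hidden.** Enrolment status is its own secondary outcome, the Effectiveness section lists retention separately from infractions, and an event that triggers exit occurs during treatment and is captured.
- **Counties.** A reader might infer that a county that expels quickly would look better. The plan pools counties (Preliminary analyses) and proposes no such comparison.
- **Analysis detail.** Denominators for infractions and screens, or a composite with exit, are choices commonly left to an analysis plan, and their absence here is no fault.
- **Consequence.** With no comparator there is no treatment contrast to bias, and the one stated model that uses program-level outcomes is optional.

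This does not remove the core point. The limit on substance use is stated, not omitted, and seeing that a client has left does not recover use or arrest that was never asked about.

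**Conclusion.** The point holds in a limited form. As written, substance use after leaving TN-ROCS, and probably arrest, goes unrecorded for clients who have left but are still interviewed, so both are understated in that group. This rests on reading treatment as TN-ROCS participation and, for arrest, on the closing clause governing the whole list.

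The size cannot be determined from the plan. The 5% to 33% range depends on assumed shares of leavers among those interviewed, exit at mid-window and assumed rate ratios. It is an illustration for substance use or arrest and does not apply to infractions, which have no post-exit events to miss.

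The documents do not support the stronger claim that early failure as such is turned into a favourable result: exit is recorded in its own right, and unreached leavers have missing events. Severity is low, because these are secondary outcomes in a single-arm pilot whose primary goal is feasibility and acceptability.

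**What to change.** 1. In the Study design overview and in Secondary client outcomes, drop the in-treatment limit for substance use and arrest. Ask every client reached about both over the same fixed window up to the 3-month interview, whether or not still enrolled. For these two outcomes, treatment then needs no definition.
2. For infractions and positive screens, which need enrolment, record the program exit date. Report them beside program exit or per enrolled month. The reporting form can be left to the analysis plan, but the date has to be collected: enrolment status at 1 and 3 months does not give time at risk exactly.

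The cost is a wording change in two places and one added item at interviews already planned, with the exit date also available from CJLs where they are already asked about enrolment. The small downside is that reported levels of substance use and arrest will look less favourable.
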